#### Secondary outcomes

Combined effect on daily functioning and overall survival based on a joint model of survival and ALSFRS-R total scores.Daily functioning, defined as mean change from baseline in ALSFRS-R total score. Disease progression will be monitored using the ALSFRS-R, which is a validated 12-item questionnaire designed to evaluate the functioning of respiratory, bulbar, fine and gross motor function in ALS patients [22]. The total score ranges from 48 (no limitation in daily activities) to 0 (total inability). The ALSFRS-R slope, the difference in scores standardized for time, is often used as measure of disease progression in clinical trials and is significantly associated with survival [23].Respiratory function, defined as mean change from baseline in Slow Vital Capacity (SVC). The SVC is associated with survival in ALS patients [24]. The obtained estimates of the vital capacity will be recorded in liters and standardized using the GLI-2012 reference standard [25].Change in outcome of Plasma creatinine. Plasma creatinine is a part of the safety tests and will be used as one of the secondary endpoints to monitor disease progression [26]. Plasma creatinine is well correlated with functional decline, muscle strength and is highly predictive for overall survival. Due to the effect of disease progression on plasma creatinine, Cystatin C will be used for monitoring kidney function as safety parameter [27].Clinical disease stage, defined as mean time spent in each stage of the King’s and ALS Milano-Torino staging systems. The King’s staging system is a simple clinical staging system, which defines four stages of ALS. The first three stages are defined by functional involvement of a region: bulbar, upper limbs and lower limbs. The number of regions involved gives the stage. Stage 4 is reached if swallowing (4A) or respiratory (4B) difficulty is severe enough to require intervention. This procedure takes the form of a semi-structured interview. MITOS is a similar clinical staging system, in which the stages are defined as loss of independence on the four domains of the ALSFRS-R: swallowing, walking/self-care, communicating and breathing [28]. Studies have shown that both King’s staging and the ALS-MITOS correlate with survival [29, 30].Safety based on the safety assessments including neurological examinations, clinical laboratory evaluations, vital signs and frequency of adverse events (AEs) or serious adverse events (SAEs). (S)AEs will be categorized according to the Common Terminology Criteria for Adverse Events and will be rated for severity and association with study drug.Tolerability defined as time-to-discontinuation of assigned treatment since randomization.Change from baseline in urinary P75^ECD^. P75 is a neutrotrophin receptor that is expressed after motor neural damage and excreted through the urine [31]. Hence, presence of P75^ECD^ in the urine is indicative for the degeneration of motor neurons. P75^ECD^ has been shown to increase over time in patients with ALS and correlates well with measures of functional decline. Moreover, the marker is associated as independent predictor of survival. Therefore, P75^ECD^ may have the utility as a potential pharmacodynamic biomarker and slowing of a rising urine level may be indicative of a biological effect.Change from baseline in plasma Neurofilament light and heavy chain. Neurofilament light and heavy chains in ALS are well known to be correlated with prognosis and remain relatively stable over time [32]. A change in the expression of neurofilament light and/or heavy chain may, therefore, be considered as supporting evidence of disease amelioration in ALS.Neuropsychological status, defined as change from baseline on the ECAS and ALS-FTD-Q. Approximately 35% of the patients, with ALS, experience cognitive or behavioral impairment. The cognitive and behavioral impairment may increase as disease progresses [33]. The neuropsychological status of patients will be evaluated using the Edinburgh Cognitive and Behavioral ALS Screen (ECAS) [34]. The ECAS is independent of motor disability and evaluates five cognitive domains: language functions, executive functions, and letter fluency, memory and visuospatial functioning. If available, ECAS version A and B will be alternated to prevent a training effect in patients. The questionnaire has a behavior screen with a carer interview, this part will not be performed in this study. In addition, we will evaluate behavioral disturbances using the ALS frontotemporal dementia questionnaire (ALS-FTD-Q) [35]. The ALS-FTD-Q is a validated instrument for the screening of behavioral disturbances in ALS. The ALS-FTD-Q has 25 items (including three cognitive items: memory, concentration, and orientation in time), with a 4-point rating scale; the maximum score is 100. A higher score indicates more behavioral disturbances.Global quality of life (QoL), defined as change from baseline on the visual analog scale (single-item scale) and EQ-5D. QoL will be measured using a visual analog scale (single-item scale): a horizontal line of 100 mm ranging from 0 (worst imaginable QoL) to 100 (perfect QoL) [36]. Generic QoL will be measured using the EQ-5D. The EQ-5D measures the health status in terms of five dimensions: mobility, self-care, usual activities, pain and depression. From the EQ-5D a quality-adjust life year (QALY) can be calculated, which is required for cost-utility analysis if a drug is beneficial for patients with ALS [37]. If a patient deceases during the follow-up period, the date will be recorded. If a patient reaches the criteria for respiratory insufficiency (tracheostomy or the use of non-invasive ventilation for ≥22 h per day for ≥10 consecutive days), the date this criterion was met will be recorded and the patient will no longer be part of the study. The time point for all secondary outcomes is month 24.

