### Participant timeline {13}

The participant timeline can be seen in (Table 1). Study medication administration and concomitant medication or medical procedures are continuously recorded. Adverse events are continuously monitored and documented. Serious adverse events are continuously monitored and reported.

**Table 1 Tab1:** Participant timeline

	Screening (−45 days)	Baseline	Days 7, 14, 21, 28, and 56	Month 3 (±7 days)	Month 6 (±7 days)	Month 9 (±7 days)	Month 12 (±7 days)	Month 15 (±7 days)	Month 18 (±7 days)	Month 21 (±7 days)	Month 24 (±7 days)
Informed consent	X										
Eligibility criteria review	X	X									
DNA sample (10 mL)^a^	X										
Randomization		X									
Demographic data and medical history	X	X									
Neurological examination		X					X				X
12-lead ECG		X		X			X				X
Dispense study medication		X		X	X	X	X	X	X	X	
Drug accountability and compliance				X	X	X	X	X	X	X	X
Vital signs and body weight		X		X	X	X	X	X	X	X	X
Blood sample (30 ml)		X		X	X	X	X	X	X	X	X
Blood sample (lithium level)			X	X	X	X	X	X	X	X	X
Urine sample (20 ml)		X		X	X	X	X	X	X	X	X
Pregnancy test^b^	*For WOCBP patients: at a monthly interval*										
Spirometry (SVC)	X	X		X	X	X	X	X	X	X	X
ALSFRS-R	X	X		X	X	X	X	X	X	X	X
Quality of life (VAS and EQ-5D)		X		X	X	X	X	X	X	X	X
LiSERS questionnaire			X	X							
King’s staging system		X		X	X	X	X	X	X	X	X
ECAS		X					X				X
ALS-FTD-Q		X					X				X
Optional: liquor biomarker sample		X			X		X				
Optional: CMAP scan^c^		X		X	X	X	X				
Survival data and ALS interventions^d^	X	X		X	X	X	X	X	X	X	X

^a^End-of-Study or early-termination visit

^b^Pregnancy tests can be performed by the patient themselves at home

^c^CMAP scan is only performed in the UMC Utrecht

^d^ALS interventions are gastrostomy, non-invasive ventilation, wheelchair use and tracheostomy

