## Assignment of interventions: allocation

### Sequence generation {16a}

Randomization will be done using a centralized online response system (Research Online, Utrecht, the Netherlands, and Castor EDC, Amsterdam, The Netherlands), which assigns each randomized participant a unique identification number which will be used throughout the study. Randomization sequences in the study will be in random block sizes of 3–9, and stratified for trial site and risk category (high vs. low risk; low risk defined as a TRICALS risk profile of ≤ −4.5).

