## Data collection and management

### Plans for assessment and collection of outcomes {18a}

During each clinical assessment patients will be asked about their current medication use and potential (serious) adverse events. All prescription drugs, over-the-counter medications, nutraceuticals, and herbal remedies will be recorded in the electronic case report form (eCRF). Additionally, ALS specific interventions such as gastrostomy placement, recommendation for wheelchair- and non-invasive ventilation (NIV) use will be recorded. Basic vital signs measurements (systolic and diastolic blood pressure, respiratory rate, heart rate and temperature) and body weight will be obtained. Details of all pregnancies in female patients and, female partners of male patients will be collected after the start of study drug and until conclusion of the pregnancy.

The ALSFRS-R questionnaire, the King’s- and ALS-MITOS staging will be filled out. Lung function is evaluated by using a non-invasive spirometer of the brand EasyOne to determine the Slow Vital Capacity (SVC), of which the highest of three attempts will be registered. During each follow-up period a venipuncture will be performed; approximately 20 ml will be obtained (4 tubes). All safety assessment will be evaluated locally. At baseline, Beta – HCG will be determined for female study patients. Additionally, patients will be asked to provide a urine sample. The urine sample (20 ml) will be used to screen for safety (dipstick or other method) and pregnancy.

Patients can optionally partake in lumbar punctures and CMAP scans. During the lumbar puncture, one vial (approximately 5 mL) of cerebrospinal fluid will be obtained at baseline, month 6 and month 12. Blood (serum and plasma), urine and CSF collected for biomarkers will be stored locally at −80 °C for at least the duration of the trial. CMAP scans will be made at baseline and months 3, 6, 9, and 12.

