#### General methods

The primary endpoint hypothesis tests will be 2-sided with a significance level of *α* = 0.05. Secondary endpoints will be considered exploratory, presented with 95% confidence intervals and without inferential statements. For each analysis, all available data (from first date of randomization to last follow-up) will be used.

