#### Efficacy: other study parameters

IIITime-to-recommended wheelchair utilization. For each individual, we will define an indicator variable whether the patient uses (or has a recommendation for) a wheelchair and calculate the time from randomization to wheelchair use or censoring. The endpoint will be analyzed as described for the primary analysis.IVTime spent in disease stage. Based on of the King’s, ALS Milano-Torino and Utrecht staging systems we will calculate the mean time spend in each stage during follow-up. The mean time will be compared between treatment arms.VChange from baseline in Urinary P75^EDC^. The change from baseline in Urinary P75^EDC^ will be analyzed using a mixed effects model as described under II.VIChange from baseline in Neurofilament light and heavy chain. The change from baseline in Neurofilament light chain will be analyzed using a mixed effects model as described under II.

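### The time-in-stage comparison names no baseline stage term, which gives up precision on an exploratory endpoint at no saving

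*Protocol article*

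**What the plan says.** The Secondary outcomes section lists "Clinical disease stage, defined as mean time spent in each stage of the King’s and ALS Milano-Torino staging systems". The section Efficacy: other study parameters, item IV, adds the Utrecht system, says "we will calculate the mean time spend in each stage during follow-up", and closes with "The mean time will be compared between treatment arms". It names no model, covariate or cross-reference.

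The baseline values exist. The row "King’s staging system" in Table 1 is marked at baseline and at every quarterly visit. MITOS has no row of its own there, but section {18a} says "The ALSFRS-R questionnaire, the King’s- and ALS-MITOS staging will be filled out". The Secondary outcomes section defines MITOS on the ALSFRS-R domains, and the ALSFRS-R is marked at baseline. Utrecht stage is among the calculated baseline variables.

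Randomisation is "stratified for trial site and risk category (high vs. low risk; low risk defined as a TRICALS risk profile of ≤ −4.5"). Clinical stage is not a stratum.

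General methods sets the status of the endpoint: "Secondary endpoints will be considered exploratory, presented with 95% confidence intervals and without inferential statements".

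**The concern.** King's stages 1 to 3 count the regions involved, and MITOS counts domains in which independence is lost. If patients mostly move forward through the stages, someone who enters in stage 3 contributes about zero months to stages 1 and 2, whichever arm they are in. Time in stage therefore varies between patients partly because of where they started. A bare difference in means leaves that variation in the standard error.

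At stake is the width of the intervals. The reported product for this endpoint is an estimate with a 95% confidence interval, and a baseline term would narrow it. With 57 patients on placebo, the precision is worth having.

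**Working it through.** **1. Is item IV different from its neighbours?**

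- Primary endpoint: stratified by site, adjusted for the TRICALS risk profile.
- Item I: the survival part carries the same terms; the ALSFRS-R part carries its own baseline and the baseline-by-time interaction.
- Item II (ALSFRS-R, then SVC, creatinine and quality of life): same framework.
- Item III (wheelchair): refers to the primary analysis.
- Items V and VI (biomarkers): refer to the model under II.
- Item IV: a comparison of means, with no term and no cross-reference.

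**2. The plan's own figures.** The document gives none for this endpoint. Its only sample size calculation concerns the primary endpoint. For a hazard ratio of 0.50, one-sided 0.025, 80% power and 2:1 allocation, the Schoenfeld formula gives (1.96 + 0.8416)² / [(2/3)(1/3)(ln 0.5)²] = 7.849 / 0.1068 = 73.5, so 74 events against the stated 72. That reproduces closely and has no bearing here.

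**3. Size of the precision loss.** From the document: 171 patients, 114 against 57, maximum treatment 24 months. Assumed, because the document gives no values:

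- a forward four-stage process with monthly progression rates of 0.12, 0.11 and 0.09 out of stages 1 to 3;
- monthly death rates of 0.004, 0.008, 0.02 and 0.06 in stages 1 to 4;
- a gamma frailty with mean 1 and variance 0.3, and no treatment effect;
- baseline mixes for stages 1 to 4 of 15/30/35/20%, 30/35/25/10% and 5/20/60/15%;
- follow-up of 24 months for all, or uniform on 6 to 24 months.

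Each of the six combinations was simulated 1,500 times. Variance reduction is 1 − Var(adjusted difference) / Var(unadjusted difference), with baseline stage entered as a factor. The interval width is multiplied by √(1 − reduction).

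| Time in | Variance reduction | Interval narrower by |
|---|---|---|
| Stage 1 | 48–66% | 28–42% |
| Stage 2 | 31–54% | 17–32% |
| Stage 3 | 21–30% | 11–16% |
| Stage 4 | 14–28% | 7–15% |

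Example with 24 months and the 15/30/35/20% mix: the standard errors in months go from 0.70 to 0.50, 1.07 to 0.84, 1.12 to 1.00 and 1.24 to 1.13. For stage 1, 1 − (0.50/0.70)² = 0.49.

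**4. Sensitivity.** A simpler forward process was also tried, with mean stays of 6 to 12 months per stage and mixes of 30/35/25/10%, 20/30/40/10% and 25/25/25/25%. The share of variance explained by baseline stage was:

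| Follow-up | Stage 1 | Stage 2 | Stage 3 | Stage 4 |
|---|---|---|---|---|
| Full 24 months | 44–58% | 29–45% | 11–31% | 3–23% |
| Uniform 3–18 months | 52–64% | 33–49% | 19–41% | 14–39% |

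The direction never changes. The late-stage gain depends most on the assumptions.

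**5. Bias.** Across the six combinations in step 3, the mean unadjusted difference under no effect lay between −0.04 and 0.06 months, which is zero within simulation error.

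**6. Chance imbalance.** For a stage held by a share p of patients, the SD of the between-arm difference in share under simple randomisation is √[p(1 − p)(1/114 + 1/57)]. This is 6.5 points at p = 0.2 and 8.1 points at p = 0.5, or about ±13 to ±16 points at 95%. Stratifying on risk category would lower this somewhat.

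**The case against.** The strongest case against is that item IV is silent on covariates and does not exclude them. The full protocol and analysis plan are not shown, and a covariate list for one exploratory endpoint is often left to them. The article gives no analysis at all for some other secondary outcomes, such as the ECAS, so brevity here may be condensation. It stands that the text does not forbid adjustment. A reader might infer that the trial has decided against it, and the document does not support that. But the article does state or refer to covariates for the other numbered items, and item IV followed as written is a bare comparison of means.

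Three stronger readings are tempting and should not be made.

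- A reader might infer that a chance imbalance in stage could pass for a drug effect. Under randomisation the unadjusted estimate is unbiased and its standard error already covers chance imbalance. The risk score also includes %SVC and the ALSFRS-R slope, which are plausibly related to stage, so stratifying on it limits imbalance to some degree.
- A reader might infer that baseline stage nearly determines the outcome. Under the assumptions in step 3 it accounts for about half or more of the variance for stage 1 only, and for 14–30% in stages 3 and 4.
- A reader might convert the gain into power. No test or power is planned for this endpoint, so such figures would describe a comparison the trial does not make.

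Two limits on the fix also stand. A baseline term does not deal with unequal follow-up in an event-driven trial. And Utrecht stage is symptom duration divided by predicted survival from the ENCALS model, on which the TRICALS risk profile is also based. Baseline stage and risk profile will therefore overlap heavily for that system, and the simulations do not represent it.

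**Conclusion.** The point holds as a free improvement of low severity. As written, item IV leaves out a baseline term that is already collected or derivable and that its neighbours have in one form or another. The cost is precision only: under the step 3 assumptions, intervals wider than they need be, most for stages 1 and 2 and modestly for stages 3 and 4. The comparison as planned is valid and unbiased. The direction of the gain was the same in every scenario tried. Its size rests on assumed stage mixes, transition rates and follow-up, since the document gives none.

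**What to change.** Add one sentence to item IV: for each staging system, the between-arm difference in time in stage will be estimated by regression on treatment, with baseline stage on the same system as a factor, and with the TRICALS risk profile and trial site as in the primary analysis; the adjusted difference will be reported with its 95% confidence interval. State that baseline MITOS stage is taken from the baseline ALSFRS-R if it is not recorded separately. For Utrecht stage, check the overlap between baseline stage and risk profile before fixing the terms.

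The cost is one line of wording, best settled before unblinding. It needs no new data, visits or patients.

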#### Statistical methods for secondary outcomes

ICombined assessment of daily functioning and survival, defined as death from any cause [50, 51]. A joint model will be constructed between a survival model and a longitudinal model for ALSFRS-R data to evaluate the combined effect on both endpoints simultaneously; the full testing procedure is described elsewhere [52]. In short, the survival sub-model will contain treatment allocation as covariate and will be stratified for randomization factors “trial site and adjusted for “TRICALS Risk Profile” as a continuous variable, where the baseline hazard function follows a Weibull distribution [53]. A mixed effects sub-model will be fitted for the ALSFRS-R data with a random intercept and random slope for time per individual. The fixed effects part contains: baseline ALSFRS-R, treatment, time, baseline ALSFRS-R*time and treatment*time. Time will be fitted both linearly as well as non-linearly using restricted cubic splines. The non-linear effect of time will be kept in the model only if significant. If not, fixed non-linear time will be deleted first, followed by random non-linear time. An unstructured covariance matrix will be used to model the correlations among repeated measures. A likelihood ratio test will be used to compare a joint model with the treatment terms vs. a joint model without the treatment terms, thereby estimating the combined effect on both the ALSFRS-R and mortality, irrespective of their association.IIALSFRS-R scores will be analyzed using the same joint model framework outlined above to account for the informative censoring due to patient death (i.e., mortality-adjusted progression). Here, we will use a likelihood ratio test to evaluate the time*treatment interaction from the ALSFRS-R sub-model. A similar strategy will be applied for change from baseline in Predicted %SVC, plasma creatinine, and QoL.

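### Neurofilament is referred to a model whose only evaluated treatment contrast is the slope difference, which can sit near zero when an early, sustained reduction is present

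*Protocol article*

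**What the plan says.** All references are to the protocol article.

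- **Analysis of neurofilament** (Efficacy: other study parameters, item VI): "The change from baseline in Neurofilament light chain will be analyzed using a mixed effects model as described under II". The item's heading covers light and heavy chain; this sentence names light chain only.
- **Contrast evaluated under item II** (Statistical methods for secondary outcomes): "Here, we will use a likelihood ratio test to evaluate the time*treatment interaction from the ALSFRS-R sub-model".
- **The model itself**, set out in item I of that section: "The fixed effects part contains: baseline ALSFRS-R, treatment, time, baseline ALSFRS-R*time and treatment*time". It has a random intercept and a random slope. On the shape of time it adds: "The non-linear effect of time will be kept in the model only if significant".
- **Expected behaviour of the marker** (Secondary outcomes): "Neurofilament light and heavy chains in ALS are well known to be correlated with prognosis and remain relatively stable over time", followed by "A change in the expression of neurofilament light and/or heavy chain may, therefore, be considered as supporting evidence of disease amelioration in ALS". The same section sets month 24 as the time point for every secondary outcome.
- **Status** (General methods): secondary endpoints are exploratory and are shown with 95% confidence intervals, without inferential statements.

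**The concern.** Item II is built for the ALSFRS-R, which declines steadily, so a drug effect shows as a difference in slope. Neurofilament is described differently: roughly flat, with a change in its level as the signal of interest. If lithium moved patients to a lower level within the first months and held them there, the two arms would run parallel from then on. The slope difference would be close to zero although the arms differ clearly.

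A supportive biomarker could then be reported as showing no effect when the data contain a sustained reduction. The interval for the slope difference would be correctly computed, but it would describe a quantity that does not match the stated rationale for measuring the marker.

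**Working it through.** **1. What the model can express.** With the baseline value as covariate, the arm difference at time t is

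D(t) = b_trt + b_int × t.

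Item II evaluates b_int alone. The difference at month 24, with t in years, is D(2) = b_trt + 2 × b_int.

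**2. When the marker is first seen after baseline.** Table 1 (Participant timeline) has the general blood sample at baseline and then at months 3, 6, ..., 24. The draws on days 7 to 56 are for lithium level. With baseline as a covariate, outcome rows start at month 3.

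**3. Algebra for an early fall.** If D(t) = δ at every visit from month 3 on, the model fits exactly with b_trt = δ and b_int = 0. No distributional assumption is needed.

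**4. Size under assumptions.** The protocol gives no effect size, SD or power for neurofilament, so there is no stated figure to reproduce for it. From the document: 114 and 57 patients, quarterly samples, and attrition from 72 events in 171 patients (72/171 = 42%). The 72 events are consistent with the protocol's inputs: (1.960 + 0.842)² / [(2/9) × (ln 0.5)²] = 73.5, or 74, and power at 72 events is 0.79. They enter here only as an attrition rate.

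Assumed: a full effect of −0.20 log units (exp(−0.20) = 0.82, about an 18% reduction); two-sided 0.05; SDs for intercept / slope per year / residual of 0.20/0.10/0.15, 0.30/0.15/0.20 and 0.40/0.25/0.25. Coefficients are expected generalised least squares estimates, and power is from the noncentral chi-square. Ranges run over the three SD sets.

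Outcome rows from month 3, linear time:

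| True course of the difference | b_trt | b_int per year | Power, interaction | Power, both terms |
|---|---|---|---|---|
| Complete by month 3, then flat | −0.200 | 0.000 | 0.05 | 0.68–1.00 |
| Half-life 1 month | −0.184 | −0.011 | 0.05–0.07 | 0.62–1.00 |
| Half-life 3 months | −0.115 | −0.053 | 0.16–0.51 | 0.43–0.98 |
| Steady divergence to −0.20 at month 24 | 0.000 | −0.100 | 0.42–0.96 | 0.35–0.95 |

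For the first row, the treatment term alone has power 0.75 to 1.00.

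**5. Does the spline help?** Not in this setting. With non-linear time kept and interacting with treatment, the interaction has power 0.05 for the early step and 0.06 to 0.08 for the 1-month half-life.

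**6. If baseline is also an outcome row.** Part of the step then loads on the slope, at about −0.07 log units per year. The interaction has power 0.27 to 0.78 with linear time and 0.63 to 0.99 with treatment by spline. The linear fit, however, shows a continuing decline that is not there. For the middle SD set, b_trt = −0.116 and b_int = −0.068, so the fitted month-24 difference is −0.116 + 2 × (−0.068) = −0.252, against a true −0.20.

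**The case against.** **The text does not say outright that neurofilament gets the interaction test.** Item VI borrows a model. The interaction sentence in item II refers to the ALSFRS-R sub-model, and the sentence that extends the strategy lists predicted %SVC, plasma creatinine and quality of life. The borrowed model contains a treatment term, so a level difference could be taken from it. This is a fair point. Still, the fixed-effects model is already in item I. On treatment contrasts, item II adds only the interaction, and no other contrast is named for neurofilament. The comparison with all treatment terms is described only for the combined ALSFRS-R and survival analysis in item I.

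**The worst case needs particular conditions.** Nothing in the protocol describes how fast lithium would act on neurofilament, and a stable untreated course does not imply a step under treatment. With slow onset the slope test works in part, and for steady divergence it is well suited. The text also does not exclude a baseline outcome row, although an analysis of change from baseline, which is zero for everyone at time 0, fits that reading poorly. A reader might infer that the trial would miss any neurofilament effect; the documents do not support that.

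**The endpoint is exploratory.** Rejection rates overstate the harm where no inferential statement is planned. This stands as to weight. But a confidence interval for the slope difference would still centre near zero after an early sustained fall, so the mismatch is one of estimation as well as testing.

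**Importance of the marker.** A reader might take neurofilament to be the trial's main biomarker. The protocol calls it supporting evidence and describes urinary P75ECD as the potential pharmacodynamic biomarker.

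**Conclusion.** The mismatch is real and limited in reach. As written, the named contrast for neurofilament is a slope difference, while the stated rationale concerns a change in a roughly stable level. If baseline is a covariate only and the fall has levelled off by about month 3, the expected slope difference is zero by algebra, and the interaction has power equal to alpha (0.05). Evaluating both treatment terms gives 0.68 to 1.00 for the assumed fall of 0.20 log units. Slower onset, or a baseline outcome row, gives partial detection. The zero slope needs only the timing and the covariate reading; every power figure also depends on the assumed effect and SDs.

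The consequence is a possibly misleading null on an exploratory, supportive biomarker. The primary analysis and its conclusion are not affected. The missing mention of heavy chain in the analysis sentence is a drafting slip, since the heading and the outcome definition both include it.

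**What to change.** Reword item VI for both light and heavy chain:

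- Log-transform the values and use the baseline log value as a covariate, with outcome rows from month 3.
- Keep item II's joint-model framework, so that informative censoring by death is still handled.
- Report, with 95% confidence intervals, the geometric mean ratio of lithium to placebo averaged over post-baseline visits and at month 24, derived from the treatment and treatment-by-time terms together (including the spline interaction, if one is kept). Earlier visits are optional.
- Report the slope difference as supportive.

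The cost is wording only, because blood is already drawn at baseline and every quarter, and biomarker samples are stored.

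There is a modest statistical price if the arms diverge steadily: both terms together have power 0.35 to 0.95, against 0.42 to 0.96 for the slope alone. The averaged ratio also dilutes such a pattern. With divergence to −0.20 at month 24, the eight visit differences run from −0.025 to −0.20 and average (−0.025 − 0.20)/2 = −0.1125. This is why the month-24 ratio and the slope difference should stand beside it.
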